## Abstract

**Background:**

Patient participation is an important indicator of quality care. Currently, there is little evidence to support the belief that participation in care is possible for patients during the acute postoperative period. Previous work indicates that there is very little opportunity for patients to participate in care in the acute context. Patients require both capability, in terms of having the required knowledge and understanding of how they can be involved in their care, and the opportunity, facilitated by clinicians, to engage in their acute postoperative care. This cluster randomised crossover trial aims to test whether a multimedia intervention improves patient participation in the acute postoperative context, as determined by pain intensity and recovery outcomes.

**Methods/design:**

A total of 240 patients admitted for primary total knee replacement surgery will be invited to participate in a cluster randomised, crossover trial and concurrent process evaluation in at least two wards at a major non-profit private hospital in Melbourne, Australia. Patients admitted to the intervention ward will receive the multimedia intervention daily from Day 1 to Day 5 (or day of discharge, if prior). The intervention will be delivered by nurses via an iPad™, comprising information on the goals of care for each day following surgery. Patients admitted to the control ward will receive usual care as determined by care pathways currently in use across the organization. The primary endpoint is the “worst pain experienced in the past 24 h” on Day 3 following TKR surgery. Pain intensity will be measured using the numerical rating scale. Secondary outcomes are interference of pain on activities of daily living, length of stay in hospital, function and pain following TKR surgery, overall satisfaction with hospitalisation, postoperative complications and hospital readmission.

**Discussion:**

The results of this study will contribute to our understanding of the effectiveness of interventions that provide knowledge and opportunity for patient participation during postoperative in-hospital care in actually increasing participation, and the impact of participation on patient outcomes. The results of this study will also provide data about the barriers and enablers to participation in the acute care context.

**Trial registration:**

Australian New Zealand Clinical Trials Registry ACTRN12614000340639 Trial Registration date 31/03/2014.

## Background

Active participation of patients in their care is important for ensuring safe and high quality healthcare [1]. Factors known to impact on patients’ capability and opportunity to participate in healthcare include both patient and nurse-related factors. Patient-related factors that impact on their ability to participate in healthcare include acceptance of the new patient role [2], medical knowledge [3–5], level of confidence [6, 7], knowledge related to condition [8, 9], acuity of illness, and comorbidity [2, 10, 11]. For nurses, acceptance and promotion of patient participation is influenced by issues such as the desire to maintain control [7, 12, 13], the acuity of patients’ illness [2, 14] and available time [14].

In Australia, total knee replacement (TKR) surgery is an increasingly common treatment for patients with osteoarthritis [15]. TKR surgery is performed to reduce knee pain, improve function and to improve quality of life [16]. In 2013, 48,502 knee replacements were undertaken nationally [15]. This represents an increase of 2.7 % compared to numbers reported in 2011. The majority of TKR surgeries in 2012 (76.9 %) were in private hospitals [15]. Of these, 21.5 % (*n* = 10,435) were performed in Victoria [15]. TKR surgery is a relatively common and successful procedure, but also considered one of the most painful [17] postoperatively.

In order for patients to achieve maximum benefit from TKR surgery they must commence early mobilisation of the knee joint to maximise range of movement [18]. Adequate pain management is fundamental to achieve early mobilisation and meet postoperative goals of recovery. High levels of postoperative pain intensity are linked to reduced knee mobility and prolonged recovery times [19, 20]. Poorly controlled pain postoperatively has also been associated with the development of ongoing chronic pain [21].

The complexity of the acute postoperative environment and severity of symptoms after TKR surgery may limit patients’ participation in their care, leading to variability in the quality of pain management they receive [22], and subsequently, their ability to meet postoperative recovery goals. Pain is a subjective experience [23] and in order for nurses to understand patients’ level of pain and provide appropriate interventions, patients need to be involved and actively participate in the control of their pain management [24]. Variability in the quality of postoperative pain management in the context of joint replacement surgery can have significant consequences for patients, including poor overall recovery [25], reduced physical functioning, increased length of stay [26] and an unsatisfactory patient experience [27].

To date, the majority of studies examining patient participation in their care have focused on patient participation in medical treatment decisions and self-management associated with chronic life-long illness [9, 12, 28]. Patient participation in meeting treatment goals of care during acute episodic illness is poorly understood and requires further exploration. The current study addresses this gap by using an intervention designed to facilitate patient participation in achieving adequate pain management and therefore meet the goals of recovery in the immediate postoperative period after TKR surgery. A nurse-led, multimedia animation intervention will be implemented immediately after surgery in order to increase both the capability of (through information) and opportunity for (through interaction with nurses) patients to participate in their goals of care after TKR surgery.

### Aims of the study

The purpose of this research is to design, implement and evaluate a nurse-led multimedia education intervention to improve postoperative outcomes for patients post TKR and explore the relationships between patient participation, patient experience and patient satisfaction with care.

The overall aim of this study is to test whether a nurse-led, multimedia intervention, designed to provide knowledge and opportunity for patients to participate in their acute postoperative recovery after surgery, improves their recovery.

## Methods/Design

A cluster randomised, crossover trial and simultaneous process evaluation will be undertaken using mixed-methods for data collection and analysis. In this study, each cluster refers to a hospital ward (1, 2 or 3) and the cohort refers to the group of patients admitted to the ward during a specified period of time. Two clusters, or wards, will receive both the intervention and control (usual care) conditions in separate time periods, and, in sequences that are randomised to the two wards. The third ward will act as an “overflow” ward for patients who are consented on the study but are unable to be admitted, when the wards are full, to either of the two orthopaedic wards that received randomized sequences of conditions. This third ward will receive the control condition only as we are unable to guarantee that this ward will contain 20 to 30 consented patients in a period and so assigning the intervention to this ward would have been wasteful (in terms of sample size allocation). The trial can be described as a cluster randomised crossover design [29] with two clusters and an added control cluster. The two crossover wards will be randomised to sequences of conditions to ensure that at least one ward receives the intervention and the other ward receives the control in each period. See Fig. 1 for an illustration of the study design.

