### Inpatient data collection: cluster randomisation with crossover

Patients will be admitted to one of the orthopaedic wards (clusters) through normal hospital procedures.

The wards will have been randomly assigned to a sequence of control (A) and intervention (B). The intervention, “B”, will be allocated to at least four cohorts. The intervention appears once in each period and twice in each of the two wards. Ward 1 will use the sequence ABBA and on Ward 2 the sequence BAAB and Ward 3 will be assigned AAAA (Fig. 1). Each cohort within a cluster (data collection period) will be accrued and monitored over a period for 12–15 weeks. To mitigate any risk of contamination between control and experimental groups, a wash out period (usual care on all wards, no intervention or data collection) between cohorts will be of approximately 2 weeks in duration.

Participants admitted to the control wards (A) during data collection periods will receive usual care based on the clinical pathways for TKR recovery. In addition to usual care, patient participants admitted to the intervention (B) ward during data collection will receive the multimedia intervention (via iPad™) each day, commencing on Day 1 after surgery.

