### Sample size calculation

In this study, the null hypothesis (H_o_) associated with the primary objective is that no difference exists between patients in the intervention group and the control group in terms of worst pain score on Day 3 post TKR surgery. NRS pain intensity scores will be analysed via the fitting of a linear mixed model with random effects for clusters, cohorts within clusters, and, patients within cohorts, and, fixed effects for the conditions. The F-test, conducted at the 5 % significance level, will be used to compare the average pain scores for the two conditions (intervention versus control).

The number of clusters is essentially fixed (i.e. two or possibly three wards) but the number of periods, or cohorts per ward, (2, 3 or 4) and the number of patients in each cohort (24 or 30) was selected in order to achieve 80 % power when there are at least two wards and when the difference (delta) between the average pain scores for the two conditions is 1.65 and at least 70 % power when delta is 1.5. Preliminary (unpublished) data indicate that pain scores decline by 1 to 1.5 units from day 3 to day 4 post TKR surgery and so a delta of 1.5 to 1.65 at 3 days is a similar but enhanced improvement.

Pilot data results also indicated a between-patient (i.e. within-cohort) standard deviation equal to 2 (i.e. between-patient variance component, VP, equals 4) and a grand mean equal to 7. The between-ward variance component (VW) and between-cohorts variance component (VC) were assumed to be equal to 0.025 (this was based on unpublished data for two wards assessed in the same time period).

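### Ward 3, a non-randomised control-only overflow ward, can enter the primary effect through the random-ward model

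*Protocol article*

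**What the plan says.** The Methods/Design section defines the clusters so as to include the third ward: "each cluster refers to a hospital ward (1, 2 or 3"). Randomisation covers two of them: "The two crossover wards will be randomised to sequences of conditions". The third takes consented patients who are "unable to be admitted, when the wards are full, to either of the two orthopaedic wards", and "This third ward will receive the control condition only". The section on inpatient data collection gives the layout: "Ward 1 will use the sequence ABBA and on Ward 2 the sequence BAAB and Ward 3 will be assigned AAAA".

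The Sample size calculation section states the primary analysis as a "linear mixed model with random effects for clusters, cohorts within clusters, and, patients within cohorts, and, fixed effects for the conditions", tested by an F-test at the 5% level. The same section gives the number of clusters as "i.e. two or possibly three wards". Table 4 and the total of 240 cover two wards. The Quantitative analysis section repeats the mixed model for the primary endpoint and places the estimation of period effects, and adjustment for them if needed, in a supportive analysis. None of these sections says whether Ward 3 patients count as controls in the primary comparison.

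**The concern.** A model with random ward effects draws on two sources. One is the within-ward contrast, in which Wards 1 and 2 act as their own controls; this is the randomised part. The other is the comparison of ward means. Wards 1 and 2 are under intervention half the time and Ward 3 never is, so a difference between Ward 3 and the other two is read partly as an effect of condition. No randomisation supports that second comparison: Ward 3 was assigned to control by design, and its patients reach it because the other wards were full.

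If overflow patients or overflow care go with more pain, the intervention looks better than it is; if with less pain, worse. The primary result would then mix randomised and non-randomised evidence, in a proportion set by a ward variance estimated from three wards.

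**Working it through.** **Inputs from the protocol.** VW = 0.025, VC = 0.025, VP = 4, 30 patients per crossover cohort, four periods, period effects from −1 to +1, delta 1.65, sequences ABBA / BAAB / AAAA. **Assumed**, because the documents do not give them: the Ward 3 cohort size *n*₃ (5 to 30, equal across periods) and the size of any Ward 3 difference.

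**1. The plan's own figure.** Simulating two wards and four periods with rounding to 0–10, and fitting ward and period to the eight cohort means, gives power 0.798 against the stated 0.803 for delta 1.65. All eight rows of Table 4 reproduce within 2 percentage points. Without period, the 0.803 row falls to about 0.34. Table 4 is thus a two-ward, within-ward calculation and is not in error. It does not describe a three-ward analysis with random wards.

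**2. Within-ward estimate.** The variance of a crossover cohort mean is v = VC + VP/30 = 0.025 + 0.1333 = 0.1583. The eight cohorts carry weights ±1/4, so Var_W = 8 × (1/16) × 0.1583 = 0.0792, SE 0.281.

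**3. Between-ward estimate.** Twice the difference between the mean of Wards 1–2 and Ward 3 also estimates the condition effect. With v₃ = VC + VP/n₃,

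Var_B = 4 × [(VW + v/4)/2 + VW + v₃/4].

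**4. Share of a Ward 3 difference that leaks in.** Generalised least squares gives the between-ward estimate weight w = Var_W / (Var_W + Var_B). A constant Ward 3 difference of 1 point moves the effect by 2w.

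- n₃ = 5: Var_B = 4 × (0.0323 + 0.025 + 0.2063) = 1.054; w = 0.0792/1.133 = 0.070; leak 0.14.
- n₃ = 30: Var_B = 4 × (0.0323 + 0.025 + 0.0396) = 0.3875; w = 0.0792/0.4667 = 0.170; leak 0.34.

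| n₃ per period | 5 | 10 | 15 | 20 | 30 |
|---|---|---|---|---|---|
| Leak, VW = 0.025 | 0.14 | 0.22 | 0.26 | 0.30 | 0.34 |
| Leak, VW estimated as 0 | 0.16 | 0.27 | 0.35 | 0.41 | 0.50 |
| SE, VW = 0.025 | 0.271 | 0.266 | 0.262 | 0.260 | 0.256 |

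With the variances held at these values, fitting period does not change the leak. With ward fixed, the leak of a constant difference is 0 and the SE is 0.281.

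**5. Variances re-estimated by REML, n₃ = 15, period effects −1 to +1.** Ranges are over repeated simulation runs.

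| Assumed Ward 3 difference | Bias, period fitted | Bias, period not fitted |
|---|---|---|
| 0.5 point | 0.08–0.10 | 0.21–0.24 |
| 1 point | 0.10–0.13 | 0.34–0.37 |

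Unmodelled period effects inflate the cohort variance and push the estimated ward variance towards zero, where the leak is largest. Even with period fitted and no Ward 3 difference, REML put the ward variance at zero in 54% to 58% of runs.

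**6. Scale.** One between-ward SD is √0.025 = 0.158. At VW = 0.025 it gives 0.158 × 0.14 = 0.02 to 0.158 × 0.34 = 0.05 points.

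**7. Degrees of freedom under the two remedies.** Ward and period fixed with Ward 3 kept: 12 − 1 − 2 − 3 − 1 = 5. Wards 1 and 2 only: 8 − 1 − 1 − 3 − 1 = 2. The critical t values are 2.57 and 4.30. With delta 1.65 and SE 0.281, power without rounding is about 0.99 and 0.82.

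**The case against.** The article is open about Ward 3: it calls it an added control cluster, explains the overflow role and gives a reason for not assigning it the intervention. All the power work rests on two wards and reproduces as a within-ward test. If the F-test were taken only from the cohort-within-ward stratum, a Ward 3 difference would not bias it. A full protocol or analysis plan may settle this. Nor is the lack of patient-level randomisation peculiar to Ward 3, since patients reach every ward by normal hospital procedures.

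Most of this stands, and it limits the charge. The article does not say that Ward 3 will be pooled; it defines Ward 3 as a cluster, makes clusters random and does not restrict the test. But the written model is the one a reader would fit, and the safe reading must be inferred from the power table.

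A reader might also infer a bias of about a fifth of delta (0.35/1.65 = 21%). That needs both a 1-point Ward 3 difference, more than six times the plan's ward SD, and the omission of period, which is a separate matter. The documents support neither the size nor the direction of such a difference. Nor did the simulations with no intervention effect show type I error above 5% (range 1.1% to 4.8%).

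**Conclusion.** The point holds as a should-fix. As written, the primary model lets a non-randomised contrast between Ward 3 and Wards 1–2 into the condition effect, at about 14% to 34% of any systematic Ward 3 difference when VW is 0.025. For assumed differences of 0.5 to 1 point and 15 patients per Ward 3 cohort, the bias is about 0.1 point (6% of delta 1.65) with period fitted, and about 0.2 to 0.35 without. For a difference of one ward SD it is negligible.

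This rests on Ward 3 patients being included as controls, on assumed Ward 3 cohort sizes and on assumed differences. The documents do not show that overflow patients differ, so they do not support saying that the result will be biased or that the trial is invalid. What they do show is that the primary analysis does not confine itself to the randomised comparison, although doing so costs little.

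**What to change.** In the primary model, fit ward and period as fixed effects, so that a constant Ward 3 difference cancels and the condition effect comes from within-ward contrasts on Wards 1 and 2. Report the analysis that pools Ward 3 through random wards as a sensitivity analysis only. The change is one of wording. It should be made before analysis, since the Trial status section says data collection is in its last phase.

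The cost is a small rise in the standard error, to 0.281 from 0.256–0.271. A limit remains: if Ward 1 and 2 cohorts are unequal, single Ward 3 cohorts receive small weights (up to about 0.025 in an example with cohorts of 20 to 35). These sum to zero, so a constant difference still cancels, but one that changes over time may not cancel fully.

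Restricting the primary analysis to Wards 1 and 2 also removes the bias and matches the basis of Table 4. It is not equivalent: it leaves 2 rather than 5 residual cohort-level degrees of freedom. Keeping Ward 3 gains those degrees of freedom only by taking its cohort-to-cohort variation as comparable with that of the crossover wards. The plan should state which option is primary.

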**Fig. 1 Fig1:**
[figure not shown]
Study design

### Setting

The study will take place in one Victorian non-profit private health service.

### Participants

Patients undergoing primary Total Knee Replacement (TKR) surgery are a high volume patient group at the participating health service. Patients after TKR who participate in their postoperative management are highly likely to benefit from participation in their postoperative recovery and these patients also have a high incidence of high intensity postoperative pain [20].

Inclusion criteria*:* Adults, aged 18 years or more, with a planned elective admission for primary TKR surgery, who are able to provide written, informed consent and complete English language questionnaires.

### Recruitment of patient participants

Recruitment will take place prior to surgery to allow potential participants time to reflect and seek clarification of their proposed involvement as well as to allow for baseline data collection. Recruitment of patient participants will take place using the method described below:

#### Method – preadmission clinic recruitment

At the participating hospital, the usual practice is the preadmission clinic coordinator contacts all patients scheduled for TKR prior to their attendance at the clinic and/or admission for surgery. At this time the coordinator will explain to patients they may be approached at the clinic about possible participation in a research study.

Wherever possible a member of the research team will attend the clinics and liaise with the clinic coordinator to identify potential participants. Suitable patients will be approached by the researcher who will invite them to read a study information sheet. Those interested in participation will be provided with a Participant Information and Consent Form and the baseline questionnaire.

### Multimedia goals of care intervention

The multimedia program was developed specifically for TKR patients by Enlighten Health®, a medical multimedia production company specialising in validated content for patient and clinical education. The multimedia intervention is presented in a format that combines text, sound, graphics and animation to provide information to patients in relation to postoperative recovery and goals of care for each day, up to 5 days following a TKR.

The multimedia program intervention, is designed to be both nurse-led, where the nurse assists the patient to navigate through the program, and patient self-directed; it is delivered to patients as a stand-alone program package on an iPad™. The intervention is designed with tailored information about the expected postoperative recovery on each day from Day one (1) to Day five (5) (or day of discharge) after TKR surgery. Embedded throughout the program is the importance of adequate pain management in order to achieve daily goals of recovery. The aim of the intervention is to facilitate an interaction between patients and their nurse each postoperative day about the specific goals and plans of care for each day of recovery after TKR surgery. The three main goals of recovery for patients after TKR surgery are: 1) to manage pain, 2) promote mobility of the knee joint to improve function and 3) avoid complications such as thromboembolism [16].

#### Intervention application procedure

Daily, until discharge from the ward, following nursing handover and after patients’ morning meal (approximately 0900 h), the nurse allocated to care for a patient enrolled in the study reminds the patient to view the corresponding day’s goals of care package on the iPad™. The iPad™ is secured to the patient’s bedside to allow easy access to the program any time of the day or night and in addition, patients’ relatives can also view the presentation. It is anticipated that after viewing the goals of care animation, patients together with the nurse will discuss the patient’s goals for the day.

### Control – usual care

The control condition, received by a cohort of patients admitted to a ward over a particular time period, consists of usual care based on the clinical pathways currently in use across the organisation for patients after TKR surgery.

### Research setting

Data will be collected in three acute inpatient orthopaedic wards of a major, private, metropolitan hospital in Melbourne. The wards comprise a total of 79 acute orthopaedic beds and provide care for approximately three new patients undergoing a TKR per day on two wards with the third ward utilised as ‘overflow’. The units are staffed with teams of specialist nursing, medical and allied health staff to manage orthopaedic conditions.

